**Figure 1 Fig1:**
[figure not shown]
**Process of recruitment, consent, randomization, treatment and measurement.**

#### Part Two, randomised controlled trial and randomisation process

Written informed consent for Part Two will be gained by the research assistant. Participants will then be randomised using concealed allocation to receive an injection from either the physiotherapist or the orthopaedic surgeon. The computer-generated randomisation sequence will be developed using Excel software by one investigator (LB) who will conceal the schedule from both the treating practitioners and the outcome assessor. Participants will be given a sealed opaque envelope by the research assistant, containing a standardised treatment sheet. This will direct the participant to one of two treatment rooms (Room A or Room B). The professional affiliation of the treating practitioner in each room will be unknown to both the study participants and the outcome assessor. Following participant randomisation to a treatment room (that is, a treating practitioner), the participant will provide written informed consent for the procedure before receiving the injection.

### Blinding

Throughout Part One the surgeon and the physiotherapist, blind to each other’s findings, will assess participants independently, in separate rooms. Participants will be blind to the profession of surgeon and the physiotherapist at all times throughout the entire trial. The outcome assessor will also be blind to the treating practitioner. Physiotherapists providing post-injection care will be asked to not seek information regarding the profession of the injecting clinician and not discuss the identity or profession of injecting clinicians with participants. They will be asked to report any breaches in blinding to the research assistant. The success of blinding will be assessed immediately post-injection, and at 6 and 12 weeks, when participants and the outcome assessor will each be asked to tick whether they think they received their injection from the physiotherapist or the surgeon. Unblinding of a participant will only be permitted in the event of an adverse event requiring management by the orthopaedic surgeon.

### Interventions

#### Injection delivered by surgeon or physiotherapist

Participants will receive, from either the physiotherapist or the surgeon, 1 ml betamethasone (Celestone Chronodose; 5.7 mg/ml) mixed with 5 ml 1% lignocaine hydrochloride, delivered to the subacromial space via an aseptic injection technique. Methylprednisolone acetate (1 ml; Depo-medrol; 40 mg/ml) will be used as an alternative, and recorded as such, if Celestone is unavailable. Standard post-injection advice will be given verbally and through a written information sheet advising reduced activity for 1 week, attendance at physiotherapy, as well as recognition of, and reporting procedures, for any adverse reactions.

#### Physiotherapy

All participants who were injected will be referred for a course of physiotherapy within the hospital’s outpatient physiotherapy department, beginning approximately 1 week post-injection. The injecting physiotherapist is not part of this department and will not provide post-injection treatment. Treating physiotherapists will be middle to senior outpatient staff with experience in treating musculoskeletal conditions. The treating physiotherapists will develop a consensus regarding best practice exercise and manual therapy interventions used for shoulder pain. Treatment will be delivered pragmatically with specific interventions and the number of sessions at the discretion of the treating physiotherapist. All treating physiotherapists will be directed to not deliver acupuncture to participants and this will be monitored by the research assistant.

### Outcome measures

Outcomes will be measured at baseline, and at 6 and 12 weeks follow-up by the blinded assessor. These time points were chosen on the basis of a previous study evaluating subacromial corticosteroid injection that found greater improvements in the injection group at 6 weeks than at 12 weeks
[27]. At baseline the demographic, service, economic disease burden and clinical data will be recorded, including age, gender, duration of condition, imaging findings, dominant arm, affected side, medicines, occupation, shoulder-related direct and indirect costs, and usual service waiting time for care. Outcome measures and time points are displayed in Table 
1.

**Table 1 Tab1:** **Outcome measures and time points**

Outcome measure	Part of study		Time point (weeks)		
	Part one	Part two	0	6	12
Shoulder Pain and Disability Index	Yes	Yes	Yes	Yes	Yes
Impact and costs questionnaire	Yes		Yes		
Work Productivity and Activity Impairment Questionnaire	Yes		Yes		
Work Limitations Questionnaire	Yes		Yes		
Usual waiting time	Yes		Yes		
Examiner agreement	Yes		Yes		
European Quality of Life, five dimensions, five levels	Yes	Yes	Yes	Yes	Yes
Pain severity visual analogue scale	Yes	Yes	Yes	Yes	Yes
Range of movement/pain pre- and post-injection		Yes	Yes		
Adverse events		Yes	Yes, throughout		
Global perceived improvement		Yes	Yes	Yes	Yes
Satisfaction visual analogue scale		Yes			Yes
Post-injection physiotherapy		Yes			Yes
Labour costs		Yes			Yes
Medicine use	Yes	Yes			Yes

The table indicates which outcome measures will be used in each part of the trial and when each outcome measure is collected.

### Primary outcome measure

The primary outcome measure will be the Shoulder Pain and Disability Index (SPADI) measured at baseline, and at 6 and 12 weeks post-injection. The SPADI is a self-rating tool consisting of 13 questions with a scale of 0 to 10, divided into pain (five questions) and disability (eight questions) subscales. The two subscales are scored separately; an overall score is then calculated from the means of the two subscale scores, resulting in a total score varying from 0 (best) to 100 (worst)
[28]. It has been widely used in shoulder research and has been shown to be reliable and valid, including use in patients with subacromial impingement syndrome of the shoulder
[28, 29].

### Secondary outcome measures

#### Economic disease burden at baseline

An impact and costs questionnaire has been developed to gather shoulder-related direct and indirect costs including medical care, work earnings, impact and absence, and also costs of personal assistance required from others. A 3-month recall period was chosen based on previously reported patient accuracy in recall over this period
[30, 31]. Impact on work productivity will be further assessed with two work productivity instruments which are validated in this patient population
[32]. The Work Productivity and Activity Impairment Questionnaire has been used in many musculoskeletal conditions, is compatible with economic costing, and is easy to administer. The Work Limitations Questionnaire
[33] is a widely used presenteeism measure with excellent construct validity and the benefit of being expressed as a percentage of productivity loss for dual clinical and economic analyses.

#### Usual waiting time for care

At the time of initial appointment for assessment, the usual waiting time to see the orthopaedic surgeon and the physiotherapist will be obtained from the hospital waiting list database.

#### Examiner agreement

The two examiners (physiotherapist and orthopaedic surgeon) will record their assessment, diagnosis, injection safety and management findings on standardised assessment forms.

#### Health-related quality of life

The European Quality of Life (five dimensions, five levels; EQ-5D-5 L) will allow quality of life to be expressed as utility values varying from 0 to 1, with 1 representing perfect health. This widely used scale builds upon the earlier EQ-5D-3 L
[34] version.

#### Pain severity

A 100 mm visual analogue scale (VAS) anchored by “no pain” (0 mm) to worst pain imaginable (100 mm) will be used to rate participants “worst pain over the last 3 days”. The VAS has established validity and reliability, with extensive use in adults
[35] and shoulder disorders
[36].

#### Range of movement and pain immediately pre- and post-injection

Within a period of 20 minutes before and 20 minutes after injection, the blinded outcome assessor will measure shoulder range of movement three times in the scapular plane with a goniometer. The instruction will be to “take your arm up as far as you feel able”. Following the three measurement trials the participant will then rate on a 100 mm VAS anchored by “no pain” (0 mm) and worst pain imaginable” (100 mm) the severity of their worst pain and their mean pain during these three trials.

#### Adverse events

Participants will be instructed via the standardised post-injection information sheet to report any unwanted side-effects or adverse events to the research team. All adverse events will be recorded. A serious adverse event will be defined as one that requires hospitalization, results in persistent incapacity, or requires antibiotic treatment for infection, related to the injection, or anything worse.

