#### Data and adverse event management

Adverse events reported by participants will be brought to the attention of the orthopaedic surgeon for clinical management as deemed appropriate. A Data Safety Monitoring Committee has been established comprising health service clinicians and experienced university academics, none of whom are involved in the study. Serious adverse events will be reported directly to both the Data Safety Monitoring Committee and the Human Research Ethics Committee. The biostatistician ([name]) will monitor the progress of the trial through interim statistical analyses at approximately one- and two-thirds completion. If the number of interim analyses is not small (for example, over five), the overall type I error rate could be controlled by adopting a higher level of significance for each interim statistical test
[40]. Alternatively, a more formal alpha spending function approach
[41] could be used to allocate some of the pre-specified overall type I error to each interim analysis. The interim analyses will be made available in confidence to the Data Safety Monitoring Committee and the Human Research Ethics Committee. The Data Safety Monitoring Committee will have authority to recommend trial cessation to the Sponsor.

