In summary, several knowledge gaps will be addressed by this research. It will evaluate the safety, feasibility, and cost of physiotherapists injecting in an Australian setting. To our knowledge, it will also, for the first time, compare the decision-making processes and clinical efficacy surrounding injection by a physiotherapist to that of a consultant orthopaedic surgeon, for a specific orthopaedic condition. We believe this to be the first study of a physiotherapist injecting corticosteroid in Australia, and it could serve as a benchmark from which subsequent studies can be conceived to further our understanding of the potential health benefits of extended-scope activity within physiotherapy, as well as other allied health professions.

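### The only adverse-event collection the article describes is participant-initiated report, with no standard enquiry at the existing post-injection, 6- and 12-week contacts, and the serious-event definition is unclear about relatedness

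*Protocol article*

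**What the plan says.** The Adverse events section gives one way for events to reach the trial: "Participants will be instructed via the standardised post-injection information sheet to report any unwanted side-effects or adverse events to the research team". It adds "All adverse events will be recorded". The Interventions section says post-injection advice is given both verbally and in writing and covers how to recognise and report reactions. The Data and adverse event management section keeps the same starting point: "Adverse events reported by participants will be brought to the attention of the orthopaedic surgeon for clinical management as deemed appropriate". Table 1 lists adverse events for Part Two as "Yes, throughout", with no separate 6- or 12-week entry.

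An event is serious if it "requires hospitalization, results in persistent incapacity, or requires antibiotic treatment for infection, related to the injection, or anything worse". The consequence of that label is that "Serious adverse events will be reported directly to both the Data Safety Monitoring Committee and the Human Research Ethics Committee".

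On purpose, the closing summary of the Discussion says of the research: "It will evaluate the safety, feasibility, and cost of physiotherapists injecting in an Australian setting". The opening of the Discussion also names safety among the matters on which the findings will inform policy makers and regulators.

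**The concern.** An instruction to report depends on the participant recognising an event, judging it worth mentioning and making contact. Mild or short-lived reactions are the easiest to lose. Recording every event governs what happens to reports that arrive; it does not find events that nobody mentions.

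The Background criticises earlier reports of no adverse events after physiotherapist injection as limited to observational data. If this trial also found few or none, a reader could not tell a low event rate from low reporting. Equal under-capture in both arms shrinks an absolute difference, and so favours a conclusion that the two injectors are alike.

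The second issue is the phrase "requires antibiotic treatment for infection, related to the injection, or anything worse". The mention of relatedness is set off by commas and can attach to infection alone or to the whole list. Because the label decides what goes directly to the two committees, the wording affects oversight.

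**Working it through.** **1. Contacts set against stated enquiries.**

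| Contact with the blinded assessor | Measures described | Adverse-event question described? |
|---|---|---|
| Within 20 minutes after injection | Range of movement, pain; blinding question | No |
| 6 weeks | SPADI, EQ-5D-5L, pain VAS, global change; blinding question | No |
| 12 weeks | As at 6 weeks, plus satisfaction and medicine use | No |

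Participants are already asked a standard question, the blinding check, at all three points. Medicine use at 12 weeks could reveal an antibiotic course, but not an event that needed no medicine.

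**2. Inputs.** The article states no adverse-event rate, capture fraction or safety sample size, so there is no safety figure to reproduce. The arm size comes from Sample size: 54 evaluable / (1 − 0.15) = 63.5, rounded up to 64, or 32 per group. This agrees with the article. The true risk *p* and the captured fraction *c* below are assumptions, shown over a range.

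**3. Chance that an arm of 32 records no event.** With independent participants, P(0) = (1 − c·p)^32. For example, (1 − 0.10)^32 = 0.034, (1 − 0.05)^32 = 0.194 and (1 − 0.025)^32 = 0.445 (0.4448 before rounding).

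| True risk p | c = 100% | c = 75% | c = 50% | c = 25% |
|---|---|---|---|---|
| 2% | 0.52 | 0.62 | 0.73 | 0.85 |
| 5% | 0.19 | 0.29 | 0.44 | 0.67 |
| 10% | 0.03 | 0.08 | 0.19 | 0.44 |

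**4. What zero events would exclude.** With complete capture, the one-sided 95% upper limit for 32 participants is 1 − 0.05^(1/32) = 0.089. If half of events were captured, the same limit applies to c·p, so the limit for the true rate is 0.089 / 0.5, about 18%. The 8.9% is due to sample size alone; only the widening is due to ascertainment.

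**5. Effect on a difference.** If both arms share the same *c*, the recorded difference is c × (true difference). Assumed true rates of 10% and 30% differ by 20 points. At c = 50% they are recorded as 5% and 15%, a difference of 10 points. With 32 per arm, a two-sided 0.05 test has power of about 52% at full capture and 26% at half capture (normal approximation). The ratio of the rates stays at 3.

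**6. The two readings of the serious-event definition.**
- If relatedness qualifies infection alone, a hospitalisation judged unrelated is serious and is reported directly.
- If it qualifies the whole list, the same hospitalisation is not serious and does not go by that route.

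Under either reading, relatedness enters at least the infection criterion. The passages quoted name no one to judge relatedness.

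**The case against.** The strongest reply is that this is a condensed article. The ethics-approved protocol (version 4) is not shown, and the wording of a visit form is the kind of detail an article leaves out. Nothing says participants are not asked at visits. Advice is also given verbally, and physiotherapy, the global rating and the medicine record are other occasions on which an event could surface. This stands in part: it cannot be asserted that events are captured only when volunteered, or that they will be under-counted. It does not remove the point. The article does name a collection method, in several places, and the method it names each time is participant report.

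Several stronger readings are tempting but unsupported:

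- *Bias in favour of the physiotherapist.* Both arms use the same route and participants are blind to the injector's profession throughout, so no differential bias is evident.
- *The surgeon filters or adjudicates events.* Reports go to the research team. The surgeon is told of them for clinical management, and no passage gives the surgeon a role in judging causality or seriousness.
- *Serious is defined as related.* That is one reading. Restricting the phrase to infection is at least as natural. General recording is unaffected either way, since all events are to be recorded.
- *The committee sees serious events and nothing else.* It also receives the interim analyses.
- *A planned safety comparison is compromised.* The article specifies no formal between-arm safety test, and the aims in the Background do not list safety. Its evaluation is promised in the Discussion.

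It is also fair to say that 32 per arm limits any safety statement even with perfect ascertainment.

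**Conclusion.** The concern holds in a limited form. Followed as written, the article would have the trial measure adverse events by volunteered report, with no standard enquiry at contacts that already take place. This may lower absolute rates in both arms and pull a true difference towards zero, in a trial that says it will evaluate safety.

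The size cannot be known from the document. The increases in the chance of zero recorded events, from 3% to 19% and from 19% to 44%, rest on an assumed 50% capture and assumed true rates of 10% and 5%; the table shows how they move under other assumptions.

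The serious-event wording is ambiguous. It is not shown to be wrong, but it matters because it controls direct reporting to the two committees. The sample size of 54, or 64 with drop-out, is unaffected. This is a cheap improvement, not a flaw in the primary analysis.

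**What to change.** Have the blinded assessor ask every participant one standard adverse-event question immediately after injection, at 6 weeks and at 12 weeks, in addition to spontaneous reports, and show those time points in Table 1. If the full protocol already does this, say so in the Adverse events section. Recruitment has begun, so document the date of the change, so that events collected before and after it can be told apart.

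Reword the serious-event definition so that seriousness does not depend on relatedness, and record relatedness as a separate item.

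The cost is a few minutes at existing contacts and one more item to record, with no extra staff or visits. More minor events will be recorded. The committees may also receive somewhat more reports, including some that prove unrelated to the injection.

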#### Global perceived improvement

We will use a five-point Global Rating of Change scale, varying from completely recovered to much worse, to capture the participants impression of overall change in their shoulder condition. The Global Rating of Change has commonly been used for this purpose in painful shoulder conditions
[37].

#### Satisfaction

Participants will be asked to rate their satisfaction with care over the 12-week period. A 100 mm VAS anchored by “not satisfied at all” (0 mm) to “completely satisfied” (100 mm) will be used.

#### Post-injection physiotherapy

The number of physiotherapy sessions provided for post-injection participants will be obtained from hospital booking systems.

#### Costs

Labour costs will be obtained from standard health service wage scales
[38] for the assessing/injecting physiotherapist, the orthopaedic surgeon, and post-injection physiotherapy care. Participant medicine use will be recorded by the blinded assessor and costs taken from the Pharmaceutical Benefits Scheme database
[39].

### Governance

#### Approvals

Ethical approval (Protocol version 4) and Site Specific Approval has been obtained through the Gold Coast Hospital and Health Service Human Research Ethics Committee, NHMRC code EC00160 (HREC/12/QGC/30; SSA/12/QGC/97), and Griffith University Human Research Ethics Committee (MED/23/13/HREC).

The research design requires that the physiotherapist act beyond the scope of usual professional practice in Australia and consequently a number of checks and approvals were required. These included legislative Approval under Queensland’s Health (Drugs and Poison) Regulation 1996, credentialing of overseas prescribing and injecting training against equivalent Australian standards, credentialing under Queensland’s Allied Health Framework for New/Complex practice, in addition to local hospital approvals.

#### Data and adverse event management

Adverse events reported by participants will be brought to the attention of the orthopaedic surgeon for clinical management as deemed appropriate. A Data Safety Monitoring Committee has been established comprising health service clinicians and experienced university academics, none of whom are involved in the study. Serious adverse events will be reported directly to both the Data Safety Monitoring Committee and the Human Research Ethics Committee. The biostatistician ([name]) will monitor the progress of the trial through interim statistical analyses at approximately one- and two-thirds completion. If the number of interim analyses is not small (for example, over five), the overall type I error rate could be controlled by adopting a higher level of significance for each interim statistical test
[40]. Alternatively, a more formal alpha spending function approach
[41] could be used to allocate some of the pre-specified overall type I error to each interim analysis. The interim analyses will be made available in confidence to the Data Safety Monitoring Committee and the Human Research Ethics Committee. The Data Safety Monitoring Committee will have authority to recommend trial cessation to the Sponsor.

#### Dissemination

Each participant will be mailed a plain language summary of the research results. Results will be also disseminated through publication, professional networks, meetings and conferences.

### Sample size

Assuming α = 0.05, β = 0.2, and a standard deviation of 21.7 point change in SPADI scores from baseline, we estimate that 54 participants (27 per group) will be required to test for comparative efficacy between the two treatments with a non-inferiority margin of 15 points in SPADI scores. This margin is specified based on clinical judgment and is approximately two-thirds of the minimum clinically important difference of 23.1 points for the SPADI at 6 weeks
[29]. The standard deviation is obtained by adding 25% to the reported standard deviation for the change in SPADI scores at 6 weeks from baseline in a previous study comparing the responsiveness for SPADI and several indices in patients with shoulder pain receiving corticosteroid injection
[42]. The power calculation is conservative in the sense that it ignores the added power inherent in the repeated measures design (assuming a first-order autoregressive covariance structure with a within-subject correlation coefficient of 0.5, the same sample size will have an increased power of above 90% using a generalised estimating equation (GEE) approach
[43] for testing the difference in changes in scores between groups with two repeated follow-up measurements
[44]). However, it is appropriate when treatment comparisons at the two individual time points (6 weeks and 12 weeks) are performed to assess the interaction treatment effect at different time after the injection. Allowing for a drop-out rate of 15%, we will recruit a total of 64 participants (32 per group) for injection. We anticipate this will require us to assess approximately 256 participants in total, because we estimate that 25% of participants assessed will be randomised for injection. This estimate is based on a study in which an orthopaedic surgeon sent 38% of patients for subacromial injection
[8]. We anticipate some practitioner disagreement will bring the final figure to approximately 25%.

